## Abstract

**Background:**

Alzheimer’s disease is a progressive neurodegenerative disease. Although some of the current treatments offer some symptomatic relief, this disease cannot be cured at present. Electroacupuncture may be effective for Alzheimer’s disease for cognitive function, but the evidence for its effectiveness is still limited. The aim of this study is to evaluate the add-on effect of electroacupuncture to donepezil for improving the cognitive function of Alzheimer’s disease.

**Methods/design:**

A total of 334 participants with Alzheimer’s disease will be randomly assigned to either an electroacupuncture combined with donepezil group or a donepezil group with a ratio of 1:1. Participants in the electroacupuncture combined with donepezil group will receive electroacupuncture in addition to donepezil for 12 weeks and will keep taking donepezil for the following 24 weeks. Participants in the control group will take donepezil only. The primary outcome is the change from baseline in the total score of the Alzheimer’s Disease Assessment Scale-cognition at week 12. A follow-up will be conducted 24 weeks after the treatment.

**Discussion:**

We expect to verify the hypothesis that acupuncture in addition to donepezil is better than donepezil in improving the cognitive function of patients with Alzheimer’s disease. This trial has a limitation that participant blinding is impossible.

**Trial registration:**

Clinical Trials.gov: ID: NCT02305836. Registered on 13 November 2014.

**Electronic supplementary material:**

The online version of this article (doi:10.1186/s13063-017-2052-y) contains supplementary material, which is available to authorized users.

## Background

Alzheimer’s disease (AD) is a neurodegenerative disease characterized by an insidious onset and a progressive impairment of cognitive function [1]. The ongoing decline of cognitive function leads to a high risk of disability which is a significant burden for patients and caregivers around the world. The incidence of AD increases in people over 65 years of age, with a prevalence of 4.8% in this age group and representing approximately 60–80% of dementias [1, 2]. Moreover, the health costs associated with AD, the reduced quality of life, and the increased risk of mortality severely affects the social development and quality of family life of AD patients [3–5].

Although some of the current treatments offer some symptomatic relief, this disease cannot be cured at present [6]. Cholinesterase-inhibitors (CIs) donepezil, rivastigmine, and galantamine are recommended for clinical use according to the guideline of The National Institute for Clinical Excellence (NICE, now National Institute for Health and Clinical Excellence) [7]. The glutamate receptor antagonist memantine has also been approved and recommended by the Food and Drug Administration (FDA) to treat moderate to severe AD [8]. CIs have modest symptomatic but not curative effects [9] and these classes of drugs have considerable adverse reactions [10, 11]. Some studies [12–14] have shown that acupuncture may be effective for improving the cognitive function of AD patients; however, because of the lack of rigorous randomization and adequate sample size, there is still not enough evidence to show the effectiveness of acupuncture. This trial aims to determine the effectiveness of electroacupuncture (EA) as an adjuvant therapy for donepezil in improving the cognitive function of patients with AD.

## Methods/Design

This trial is a prospective, randomized controlled, clinical trial to be conducted between June 2017 and December 2019. Three hundred and thirty-four participants with AD will be recruited at Guang’anmen Hospital, Beijing, China via the hospital web or posters. Recruiting and screening will be in the charge of a research assistant, whereas the diagnosis will be made by a neurologist. A 2-week baseline assessment will be conducted. Randomization is performed by the pharmacological assessment center at Guang’anmen Hospital. The participants identified as eligible will be randomized into two groups—EA combined with donepezil and donepezil—at a ratio of 1:1. The random block is set to 4, and random grouping is produced by using the Statistics Analysis System (SAS) software. Random numbers and information about grouping are sealed into opaque envelopes with correlative sequence numbers of entering the trial marked on the outside. Acupuncturists will open the envelopes according to the sequence numbers. The flowchart of the trial is shown in Fig. 1. The total study period of this trial is 38 weeks (Fig. 1), including 2-week baseline assessment, 12-week treatment period and 24-week follow-up period.

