### Intervention

#### EA combined with donepezil group

The acupoints are GV 16, GV 20, GV 24, and *Shang Yintang* (up to GV 29 1 cun), as well as bilateral EX-HN 5 and KI 4. The location of the acupoints is based on the *The Name and Location of Acupoints* drafted in 2006 by the National Standard of the People’s Republic of China (GB/T 12346-2006). The acupuncture protocol is based on reviews of acupuncture for AD [18, 19] published and expert consensus. Acupuncturists who have at least 2 years of practical experience will perform the intervention. Disposable, sterilized needles made of stainless steel (Hwato, Suzhou Medical Appliance Factory, Suzhou, China) and electric stimulators (SDZ-V electroacupuncture apparatus, Suzhou Medical Appliance Factory, Suzhou, China) will be used in the treatment group. After routine disinfection, the GV 16 will be needled while participants are in the sitting position with their head slightly forward and their muscles relaxed. The needle (25 mm in length) will be inserted obliquely and slowly downward toward the mandibular direction to a depth of 12.5 mm. The needle will be immediately removed after “*de qi*” (*de qi*, which is very important to therapeutic effect, is a sensation of soreness, heaviness, and numbness when needling [20]) and not retained. *Shang Yintang*, GV 20, and GV 24 will be needled (40 mm in length) at a 30° angle to a depth of approximately 12.5 mm while participants are in the decubitus position. For bilateral EX-HN 5 and KI 4, the needle (40 mm in length) will be vertically inserted to a depth of 25 mm. The electric stimulator will be applied to GV 20, GV 24, and bilateral EX-HN 5 with a spare-dense wave of 10/50 Hz, 0.5–5.0 mA. The current intensity is set up to the maximum tolerance of patients. There are three sessions per week with each session lasting for 30 min. There will be 12 weeks of treatment with 36 sessions for each participant in total. EA treatment will last for 12 weeks.

Donepezil (Eisai Pharmaceuticals, Shanghai, China) 5 mg will be given once daily before bed-time for the first 4–6 weeks. Based on the treatment effect, the dosage may be increased to 10 mg once daily before bed-time for the next 6–8 weeks. Donepezil will be taken for continuously for 24 weeks.

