However, a limitation of this trial is that participant blinding is not possible due to the two different therapeutic strategies employed for each group. Therefore, to minimize any bias that may result from the two treatments, the process of randomization will be under strict control and the investigators and data analysts are to be blinded. Acupuncture as a complex intervention produced greater response expectancies and placebo effects [37, 38]. However, the expectancy effects of acupuncture cannot be estimated in this trial due to the impaired cognitive function of AD patients.

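### A single published block size of 4, with treating acupuncturists opening the envelopes, weakens allocation concealment: up to a third of allocations can be deduced in advance

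*Protocol article*

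**What the plan says.** Under Methods/Design, the protocol article fixes the following:

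- **One site:** "Three hundred and thirty-four participants with AD will be recruited at Guang’anmen Hospital, Beijing, China via the hospital web or posters".
- **Ratio and block:** two groups "at a ratio of 1:1", and "The random block is set to 4, and random grouping is produced by using the Statistics Analysis System (SAS) software". No second block size and no stratification factor is given.
- **Concealment device:** "Random numbers and information about grouping are sealed into opaque envelopes with correlative sequence numbers of entering the trial marked on the outside".
- **Who opens:** "Acupuncturists will open the envelopes according to the sequence numbers".
- **Who recruits and diagnoses:** "Recruiting and screening will be in the charge of a research assistant, whereas the diagnosis will be made by a neurologist".

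The same section has the hospital's pharmacological assessment center perform the randomization. The intervention section adds: "Acupuncturists who have at least 2 years of practical experience will perform the intervention". Quality control states that the research assistants who rate the scales do not know the groups. The statistical section states that the statisticians analyse blind. The Discussion accepts that participants cannot be blinded and answers that "the process of randomization will be under strict control and the investigators and data analysts are to be blinded".

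**The concern.** Opaque envelopes hide what is in the next envelope. They do not hide what the block structure reveals once earlier envelopes have been opened. With one unstratified list at one hospital, a fixed block of 4 and a published block size, the remaining allocations in a block can be worked out from those already made. The acupuncturists open the envelopes and see who receives EA, so they can follow the sequence.

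Foreknowledge matters if it affects who enters or when. Some entry criteria involve judgement, such as the emotional assessment for depression and the exclusion for failure to cooperate with examinations. The 2-week baseline period also leaves some room to shift timing. Selection bias that arises this way is not removed by masked rating, which guards against a different bias. The analysis of covariance adjusts only for baseline ADAS-cog and age, so prognosis judged on other grounds would remain. Because participants cannot be blinded, the Discussion leans partly on tight control of randomization, and that control is where this weakness lies.

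**Working it through.** The article gives no predictability figure to reproduce. Its only related figure is the sample size, checked here because the total of 334 is used below.

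**Sample size (Sample size and statistical analysis).** Inputs: 39% v 55%, two-sided 5%, 80% power. With a pooled-variance test of two proportions and no continuity correction:

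n per arm = [1.96 × √(2 × 0.47 × 0.53) + 0.842 × √(0.39 × 0.61 + 0.55 × 0.45)]² / 0.16² ≈ 151.6, so 152 per arm and 304 in total. This matches the plan. Then 304 × 1.10 = 334.4, which matches the stated 334. Block size does not enter this calculation.

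**Allocations certain in advance, fixed block of 4.** Inputs from Methods/Design: block of 4 and ratio 1:1, so each block holds two A and two B. There are 6 equally likely orders. An allocation is certain once one arm is used up within the block.

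| Order | Certain positions | Count |
|---|---|---|
| AABB | 3rd, 4th | 2 |
| BBAA | 3rd, 4th | 2 |
| ABAB | 4th | 1 |
| ABBA | 4th | 1 |
| BABA | 4th | 1 |
| BAAB | 4th | 1 |

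The total is 8 certain positions out of 6 × 4 = 24, which is 33.3%, or 1.333 per block. Since 334 = 83 × 4 + 2, and the first two positions of a block are never certain, the expected number is 83 × 4/3 = 110.7, about 111 of 334 (33.1%).

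**Best guess from known history, fixed block of 4.** The chance of being right is 1/2 at the 1st position, 2/3 at the 2nd, 2/3 at the 3rd (1/3 × 1 + 2/3 × 1/2) and 1 at the 4th. The mean is (1/2 + 2/3 + 2/3 + 1)/4 = 17/24 = 70.8%, against 50% with no information.

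**Alternatives.** The fixed-block rows are exact enumerations. The mixed rows are simulations of 334 allocations, for an observer who knows every past allocation and the set of possible sizes but not the size of the current block. The sets of sizes are assumptions, since the article gives none.

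| Scheme | Certain in advance | Best guess right |
|---|---|---|
| Fixed 4 | 33.3% | 70.8% |
| Fixed 6 | 25.0% | 68.3% |
| Fixed 8 | 20.0% | 66.6% |
| Random mix of 4 and 6 | about 5% | about 69% |
| Random mix of 4, 6 and 8 | about 2% | about 68% |

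Varying the size removes most of the certainty. It does little to the best-guess rate, which reflects the tendency of any small balanced block to correct itself. A larger fixed block also helps much less with certainty than a masked mixture.

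**The case against.** The strongest defence is the separation of roles. Selection bias requires that whoever decides entry can foresee the next allocation. Here a research assistant recruits and screens, a neurologist diagnoses, and the acupuncturists have no stated part in either. The envelopes are sealed, opaque and numbered. Randomization applies to participants already found eligible, with a 2-week baseline assessment described before it. Several entry criteria are scored thresholds (MMSE, MTA-scale), which limits discretion. Adjustment for baseline ADAS-cog and age would absorb part of any imbalance.

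Most of this stands, and it rules out several stronger readings that a reader might infer:

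- **That the acupuncturists keep the envelopes.** The text says only that they open them. Custody is not stated and may be set out in the full protocol.
- **That a third of allocations will in fact be known to those who enrol.** The third is a ceiling, reached only by someone who knows the block size and every earlier allocation.
- **That the trial is unblinded throughout.** Participants and acupuncturists know the treatment; scale assessors and statisticians are described as masked.
- **That a fixed block contradicts the Discussion's promise of strict control.** It falls short of what that promise suggests, but the two statements are compatible. The statement that investigators are blinded cannot, however, cover the acupuncturists.

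The defence does not supply a barrier. Nothing in the article prevents the acupuncturists' knowledge from passing to recruiting staff at the same hospital, or prevents the acupuncturists from influencing entry or timing.

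**Conclusion.** The point holds as an avoidable weakening of concealment. A fully informed observer could know up to one third of allocations in advance, about 111 of 334. This rests on the text as written: one unstratified list, every block of size 4, 1:1 allocation, and an observer with the complete allocation history. The acupuncturists can be such observers.

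The figure measures predictability, not bias in the change in ADAS-cog. Turning it into bias would need assumptions about leakage and steering that the documents cannot supply. A reader might infer that concealment has failed or that the result will be biased. The documents support neither, because the people who decide entry are not the people who open the envelopes. The case for changing the procedure is that the remedy is cheap, while selection bias cannot be undone after enrolment.

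**What to change.** For all remaining participants (Trial status says that recruitment is under way):

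1. Generate a new SAS list with randomly varying block sizes, for example 4, 6 and 8, and withhold the sizes from site staff until enrolment closes. Certain allocations fall from 33% to about 2%. The best-guess rate falls only from 71% to about 68–69%, so this step alone does not remove predictability.
2. Preferably, have the pharmacological assessment center, which already performs the randomization, release each allocation only after eligibility and baseline ADAS-cog are recorded, instead of having acupuncturists open envelopes. Methods/Design already places eligibility before randomization; this makes that order, and the recorded baseline, a condition of release.

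**Cost:** a new list, a small change of procedure and a submission to the ethics committee, which the article already requires for important modifications. Possible imbalance in group size grows slightly: at most half a block, so 4 participants in a block of 8 against 2 in a block of 4. Exact balance is not guaranteed now either, because 334 is not a multiple of 4. The sample size stays at 304 before and 334 after allowance for loss.

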**Fig. 1 Fig1:**
[figure not shown]
The flowchart of the trial

The trial will be conducted in accordance with the principles of the Declaration of Helsinki, and has been approved by the review boards and ethics committees of the participating hospital (Ethics approval number: 2014EC087).

## Participants

Participants meeting all of the following criteria will be included in this trial: (1) the diagnostic criteria of Neurological Communicative Disorders and Stroke and the Alzheimer Disease and Related Disorders Association (NINCDS-ADRDA) [15] or the Operational Criteria for the Diagnosis of Alzheimer’s Disease (OCDAD) [16], (2) aged between 60–85 years, (3) cognitive impairment based on the scores of the Chinese version of the Mini Mental State Examination (MMSE) (an illiteracy group ≤19, a primary school group ≤22, a junior high school and high school group ≤3, and a well-educated group ≤26) [17], (4) absence of depression (via an emotional assessment), (5) magnetic resonance imaging (MRI) confirmation of atrophy of the hippocampus or the medial temporal lobe volume, (6) the Medial Temporal Lobe Atrophy Rating Scale (MTA-scale) score (≥2 for those under 75 years, and ≥3 for those over 75 years).

Participants meeting any one of the following criteria will be excluded from this trial: (1) cognitive impairment caused by other factors (e.g., vascular dementia, dementia with Lewy bodies, frontotemporal dementia, hormone or metabolic abnormalities, hypothyroidism, folic acid or vitamin B_12_ deficiency, delirium or other mental and emotional disorders (such as schizophrenia and depression)), (2) a serious heart condition, hepatic disease, renal system disease, hematopoietic system disease, or whole-body malnutrition, (3) aphasia, disturbance of consciousness, or failure to cooperate with the related examinations due to physical disability, (4) anticoagulant treatments such as warfarin or heparin, (5) use of pacemakers, or (6) receiving acupuncture or CI treatment in the past 2 weeks.

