### Outcome measures

The primary outcome is the change from baseline in the Alzheimer’s Disease Assessment Scale-cognition (ADAS-cog) [21] score measured at week 12. The maximum score of the ADAS-cog is 70 including 15 items of cognitive dysfunction assessment. The higher values indicate higher degree of deficit [22].

The secondary outcomes include the following items: the change from baseline in the ADAS-cog score measured at week 36. The change from baseline in total MMSE score [23], in the Alzheimer’s Disease Cooperative Study-Activity of Daily Living (ADCS-ADL) score, and in the Quality of Life-Alzheimer’s Disease (QOL-AD) score measured at weeks 12 and 36. The MMSE score is commonly used for estimating the severity of cognitive impairment with a maximum score of 30. The questions in this scale included orientation to time, orientation to place, attention and calculation, recall of three words, and visual construction. The ADCS-ADL score contains 19 domains about assessment of basic and operational ability of daily living [24]. The QOL-AD score, which includes physical health, mental health, social and financial assessment, and quality of life domains, is completed by both patients and caregivers [25].

All the adverse events will be recorded and assessed throughout the whole study period. Adverse reactions related to acupuncture may be fainting, hematoma formation, local infection or skin pain. Individuals who develop severe complications will be excluded from continuing in study, and the reasons for their termination will be recorded.

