### Sample size and statistical analysis

The calculation of sample size is based on the primary outcome which is the change from baseline in the ADAS-cog score. According to previous studies [26], 39% of patients showed an improvement of at least 4 points on the ADAS-cog score after being treated with donepezil. We estimated the rate to be 39% in the donepezil group and 55% in the EA combined with donepezil group. Three hundred and four participants were needed to provide 80% power at a significant level of 5% using analysis of variance. The total sample size required for the study is 334 (167 each group) assuming a 10% loss to follow-up.

Baseline score of the ADAS-cog and age will be used as a covariate when assessing the differences between the EA combined with donepezil group and the donepezil group by an analysis of covariance for the primary and the secondary variables if data fits the normal distribution. Otherwise, a nonparametric test will be used to compare the statistical difference between the two groups. All the data will be blindly analyzed by the statisticians from the Clinical Evaluation Center of Guang’anmen Hospital. SPSS 20.0 (IBM Corp., Armonk, NY, USA) statistical software will be used for the statistical analyses. Subanalysis will be applied to the statistical analysis according to the severity of the condition of participants measured by the ADAS-cog [27]).

Efficiency and safety analysis will be based on all the participants at randomization according to the intention-to-treat (ITT) principle. Missing values assumed missing at random will be handled by the multiple imputation method [28]. Continuous data will be presented by the average and standard error. Two-sided tests will be used for all outcomes. A *P* value of less than 0.05 is considered to show statistical significance.

For the safety assessments, a description on the adverse events and adverse reactions will be presented in tables. These tables will include the categories, severity, rate of incidence, and correlation with the treatment. Individuals with serious adverse events should stop receiving the intervention and details will be reported in a timely manner.

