## Discussion

In recent years, previous studies have shown that acupuncture might be effective in improving the cognitive function of AD patients [29, 30]. The results of this study will contribute to a better understanding that whether EA has additional effects to donepezil for improving the cognitive function of patients with AD.

Although clinical diagnosis is the core criteria for AD patients, preclinical diagnostic criteria, such as bio-marker evidence for AD, are also used in clinical practice and research [17]. Medial temporal lobe atrophy (MTA) as the typical imaging appearance can differentiate AD from ageing with a sensitivity and specificity of 80–85%. The severity of MTA combined with clinical information seems justified to be taken into account when diagnosing AD in clinical practice [31]. Therefore, the included criteria of this trial are based on the degree of atrophy of hippocampal or medial temporal lobe volume (measured by MRI). Moreover, as the MTA-scale scores differentiate between moderate to severe AD patients with a sensitivity of 70–100% and a specificity of 67–96%, according to the severity of the condition of participants, subgroup analysis will be applied in the statistical analysis. Furthermore, donepezil is approved by the FDA to treat the symptoms of mild to moderate AD [24, 25] and studies have shown that it can improve the neuropsychiatric, cognitive, and global functions [32–34]. Accordingly, donepezil was chosen as a positive control in this trial. Additionally, an appraisal of drug evolution for AD has shown that the primary outcomes of trials can be described within cognitive, functional, global change, and severity domains [17]. On the basis of this appraisal, the primary outcome is the ADAS-cog score. The ADAS-cog, assessing the severity of impairment of selective areas of cognition, is a sensitive and reliable neuropsychological test [35]. Moreover, a previous trial [36] which had a similar design also evaluated the change in ADAS-cog score after treatment, but follow-up effectiveness was not assessed. Therefore, a 12-week treatment with a follow-up at 24 weeks is expected to better demonstrate the additional effect of EA to donepezil in treating AD.

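### The MMSE entry limit for the junior high and high school group is printed as ≤3 of 30, which contradicts the rising limits for the other education groups in the same sentence

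*Protocol article*

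**What the plan says.** The Participants section opens the eligibility list with "Participants meeting all of the following criteria will be included in this trial", so each inclusion criterion is binding on its own. Criterion (3) requires cognitive impairment on the Chinese version of the MMSE and gives an upper limit for each of four education groups: "an illiteracy group ≤19, a primary school group ≤22, a junior high school and high school group ≤3, and a well-educated group ≤26". Reference 17 is cited for these limits.

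The Outcome measures section fixes the scale: "The MMSE score is commonly used for estimating the severity of cognitive impairment with a maximum score of 30". The figure for the junior high and high school group appears once. No other section restates it or gives another value.

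Two other statements bear on who is meant to enter. The Discussion supports the choice of comparator by noting that "donepezil is approved by the FDA to treat the symptoms of mild to moderate AD". The statistical section plans a breakdown by disease severity: "Subanalysis will be applied to the statistical analysis according to the severity of the condition of participants measured by the ADAS-cog". The Trial status section says that recruitment is under way.

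**The concern.** An education-adjusted cut-off allows for the fact that people with more schooling tend to score higher at the same level of impairment, so the limits should not fall as schooling rises. Here they rise from the first group to the second, collapse at the third and recover at the fourth. The sentence therefore contradicts itself, and the article offers no means of recovering the intended figure.

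The figure matters because it decides who may be randomized. If it were applied as printed, one education group could enter only at the very bottom of the scale, which sits poorly with a rationale built on mild to moderate disease. Severity would then be tied to education by construction. That would carry into the baseline ADAS-cog score, which is a covariate in the primary analysis, and into the severity subanalysis. If another limit is in use at the hospital, enrolment departs from the published criterion for some patients, and a reader of the results cannot tell who was eligible.

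**Working it through.** The limit is a stated threshold and is not computed from other figures, so there is no formula to reproduce. The check is of its order and of its position on the scale.

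**Inputs.** Upper limits of 19, 22, 3 and 26, in order of increasing schooling (Participants, criterion 3). Scale maximum of 30 (Outcome measures). Assumption: scores are whole numbers from 0, which gives 31 possible values.

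**Step 1, order.** Differences between consecutive groups:
- primary school minus illiterate: 22 − 19 = +3
- junior high and high school minus primary school: 3 − 22 = −19
- well-educated minus junior high and high school: 26 − 3 = +23

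The sequence is not monotone. With the third figure set aside, 19, 22 and 26 are in order, so the third is the one that does not fit.

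**Step 2, admissible scores.** A limit of k admits k + 1 of 31 values.

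| Education group | Limit | Values admitted | Share of the scale |
|---|---|---|---|
| Illiterate | ≤19 | 20 | 20/31 = 65% |
| Primary school | ≤22 | 23 | 23/31 = 74% |
| Junior high and high school | ≤3 | 4 | 4/31 = 13% |
| Well-educated | ≤26 | 27 | 27/31 = 87% |

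The highest admissible score in the third group is 3/30 = 10% of the maximum. These are shares of the scale, not of patients.

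**Step 3, who is eligible at a given score, read literally.**
- 0 to 3: all four groups
- 4 to 19: every group except junior high and high school
- 20 to 22: primary school and well-educated only
- 23 to 26: well-educated only
- 27 to 30: none

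At scores from 4 to 19, the less educated and the more educated patient both qualify, and the patient between them does not.

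**Step 4, which patients the discrepancy touches.** Suppose that screening uses some other limit above 3. A patient in this group scoring 0 to 3 is eligible under both limits. A patient scoring above the limit in use is ineligible under both. Only those scoring from 4 up to the limit in use are treated differently from the printed text.

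**Step 5, sample size, to confirm that it is untouched.** The plan assumes rates of 39% and 55% ("We estimated the rate to be 39% in the donepezil group and 55% in the EA combined with donepezil group"), with two-sided tests ("Two-sided tests will be used for all outcomes"), 5% significance and 80% power. With mean rate 0.47:

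n per arm = [1.960 × √(2 × 0.47 × 0.53) + 0.842 × √(0.39 × 0.61 + 0.55 × 0.45)]² / 0.16² = (1.383 + 0.586)² / 0.0256 ≈ 152

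That is 304 in total, the stated figure ("Three hundred and four participants were needed to provide 80% power at a significant level of 5% using analysis of variance"), with power of 80.1%. The MMSE limit does not enter this calculation.

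**The case against.** The strongest reply is that this is an obvious misprint in an article that condenses a fuller protocol. Nothing suggests that the investigators meant to restrict one education group to scores of 0 to 3. The anomaly is visible in its own sentence, a neurologist makes the diagnosis, and MRI and MTA-scale criteria also apply. The full protocol and the screening form are not shown and may carry a sound figure. A fault in reading the text from the PDF cannot be wholly excluded either, although the sentence is intact running prose and its neighbouring figures are whole.

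Much of this stands. The point is an internal inconsistency, not a questionable design choice, and harm from literal use is possible but not shown. The criterion acts before randomization and equally on both arms, so it does not bias the between-arm comparison or alter the type I error rate. What does not follow is that the figure can be left alone. It is a mandatory limit, more than one value would fit between its neighbours, and if the full protocol differs, the published article contradicts it.

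A reader might also infer more than the article supports:
- **A large, quantifiable loss of candidates.** No education mix or MMSE distribution is given, so no percentage can be attached.
- **Little measurable ADAS-cog change in those admitted.** The article gives no link between MMSE and ADAS-cog scores. Higher ADAS-cog means greater deficit, so a very impaired patient may have little room to worsen but would still have room to improve.
- **A protocol breach for every patient in the group.** Step 4 of the working shows that only those between the two limits are affected. A single hospital recruits, so there is no question of sites differing.
- **A ready answer in reference 17.** The Discussion also cites that reference for diagnostic criteria and biomarkers and for an appraisal of drug trials in AD. Nothing shown establishes it as a validation of the Chinese MMSE.

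**Conclusion.** The limit is wrong as printed, or at the least cannot stand beside the other three. It breaks the order by 19 points downward and 23 points back up. It admits 4 of 31 scores where the other groups admit 20, 23 and 27. A dropped digit is the probable explanation, but the article does not show the intended value and none is inferred here.

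The conclusion rests on the four printed figures, the stated maximum of 30 and the rule that all inclusion criteria must be met; the scale shares also assume whole-number scores from 0. It does not rest on any assumption about how many candidates have this level of schooling. The possible effects are on recruitment, on the mix of severity by education, on the severity subanalysis and on how far the results generalize. The size of these effects cannot be calculated from the article.

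**What to change.** - Reconcile the printed limit for the junior high and high school group with the ethics-approved full protocol, with the screening form and case report form, and with the source actually used for the education-specific cut-offs. Confirm that reference 17 is that source, or cite the right one.
- Confirm that the reconciled limit is consistent in order with 22 and 26.
- Publish the corrected figure, and notify the ethics committee as the Ethics and dissemination section provides for important modifications.
- Check the eligibility of patients already screened in this education group, and record which limit was applied and from when.

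The cost is a one-figure correction, an ethics notice and a check of the screening log. The sample size and the analysis model need no change.
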